#### 2.12.2. Plans to Promote Participant Retention and Complete Follow-Up

The plans to promote participant retention and complete follow-up include: (1) delivering hand-outs with highlights at the end of each session; (2) contacting participants when no records of the smart band are detected by the IDEApp web-based platform; (3) contacting participants to remind them about the upcoming appointments and let them know what to expect from them and the estimated time frame; (4) availability and flexibility of study stuff to arrange assessment visits at convenient times; (5) developing good therapist–client alliance.

#### 2.12.3. Data Management

Study data will be collected, entered, and managed using REDCap electronic data capture tools hosted at IMIM [30], which offer a free and secure method of robust data collection. More specifically, data will be collected offline in the REDCap mobile app on an Android tablet and then will be sync back to the project on the REDCap server. A password system will be utilised to control access to data and the activity that researchers may undertake is regulated by the privileges associated with their user identification code.

Original study consent forms will be entered, stored in numerical order and kept on file in locked cabinets at the site for a period of 5 years after completion of the study. Access to the study files will be restricted.

#### 2.12.4. Confidentiality

In order to ensure participants’ confidentiality during the study and the transmission of personal data, we will set a security protocol in accordance with the local Spanish laws. A 9-digit identification number (IDN) will be generated for all the participants throughout all the phases of the study. The cross-reference of this identification number and the patient identity will be encrypted and stored in a database file kept in a computer without access to the Internet (neither by wire nor Wi-Fi). Patients will be identified by the IDN, and a random number assigned by the app, which will be the user code to access the application too. Study participants will be requested by a user or QR code when signing into the app. Personal information will not be collected by IDEApp.

All data collected by the smart band and IDEApp will be processed applying technical and organisational security measures established by the current legislation (Organic Law 3/2018, of 5th December, on Protection of Personal Data and guarantee of digital rights). The database will be stored in a physical server kept in the IMIM-Parc de Salut Mar facilities. This information will be used solely and exclusively to carry out analyses related to the objectives of the study and will be stored anonymously in a database during and after the trial.

## 3. Statistical Methods

### 3.1. Statistical Methods for Primary and Secondary Outcomes

Statistical analysis will be performed using the software SPSS Statistics 25 (IBM Corp., Armonk, NY, USA). Descriptive statistics will be used to analyse the distribution of socio-demographic and clinical characteristics among groups at baseline. Continuous variables with a normal distribution will be analysed performing an ANOVA. Where the premises of normalcy are not met, the Wilcoxon test will be used. The differences between groups on the categorical and mail clinical variables will be evaluated by using a Chi-square test. Those variables that are statistically significant may be used as covariates for a logistic or linear regression study of the factors associated with the magnitude of the effect, and determine which variables are better predictors of functioning. The effect size index will be estimated in case of correlation indexes for each of the performed analyses. To analyse efficacy, we will perform intention to treat analysis. Analysis will be two-tailed and the significance set a *p* < 0.05.

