### 2.6. Sample Size

Initially, we computed a sample size of 152, given a power of 0.8, an alpha level of 0.05 and inferring functioning according to clinical remission data [28]. To our knowledge, functioning as a main outcome for physical exercise in depression has not set a precedent to guide our calculations. Thus, we computed a Cohen’s d effect size of 0.5 to make estimations more reliable. An expected drop-out rate of 20% was set, which resulted according to the initial design in two arms of 76 subjects each. However, during the cocreative process of the intervention, it was discussed whether motivational messages of the app would mask the effect of the group sessions on the outcomes of the study. Therefore, it was decided to include a third study arm to assess the intervention without motivational elements triggered by the app. We increased the sample size by adding 20 participants, which will be distributed into the two experimental groups, leaving us with a sample size of 172.

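### The optional regression meant to find what influences the size of the effect uses covariate terms chosen by a significance filter; these can identify predictors of functioning but not effect modifiers

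*Protocol article*

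**What the plan says.** Section 3.1 of the protocol article begins with descriptive statistics to "analyse the distribution of socio-demographic and clinical characteristics among groups at baseline". It then names ANOVA for normally distributed variables and the Wilcoxon test otherwise, and adds: "The differences between groups on the categorical and mail clinical variables will be evaluated by using a Chi-square test". The next sentence gives the rule at issue: "Those variables that are statistically significant may be used as covariates", and the regression they may enter is described as a "logistic or linear regression study of the factors associated with the magnitude of the effect, and determine which variables are better predictors of functioning".

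That sentence sets three things: how variables are chosen (statistical significance), what they do in the model (covariates), and two aims (what is tied to the size of the effect, and what predicts functioning). The article names no interaction, moderator or subgroup-by-arm term anywhere. Section 2.5.1 makes (A+B) vs Control the main comparison.

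**The concern.** The two aims are different statistical questions. A predictor of functioning is a variable related to the score whichever arm the participant is in. A factor tied to the size of the effect is one across whose values the arm difference changes. One covariate regression is offered for both, and it is suited only to the first.

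The entry rule adds a second difficulty. If significant means different between the groups at baseline, then under random allocation the rule selects on chance imbalance, which carries no information about effect modification.

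At stake is the interpretation of a secondary result. An ordinary prognostic variable could be described as influencing how much the programme helps, while a real modifier would seldom be examined. The introduction and discussion give individual differences and tailored prescription as part of the trial's rationale, so readers are likely to look for such findings.

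**Working it through.** The plan gives no figure for this analysis, so there is none to reproduce.

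**Inputs from the document**
- Main comparison: 48 + 48 = 96 vs 76 (sections 2.1 and 2.5.1).
- Drop-out 20% (section 2.6): 96 × 0.80 = 76.8, so 77; 76 × 0.80 = 60.8, so 61; total 138.
- Two-sided 0.05 (section 3.1).
- Arm difference 0.5 SD (section 2.6), used in the simulations.

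**Assumptions, because the document gives no values**
- Correlation of a prognostic factor with functioning: 0.2, 0.3 or 0.5.
- A modifier's slope differs between arms by 0.5 SD per SD.

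**Step 1: what each term tests**
- Covariate model: functioning = a + b·arm + c·factor + error. The arm difference is b at every value of the factor, so the model holds the effect constant. Testing c = 0 is a test of prognosis.
- Interaction model: add d·arm·factor. The arm difference at factor value x is b + d·x. Only d describes how the effect depends on the factor.

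**Step 2: the filter**
A between-group test of a baseline variable at 0.05 rejects in about 5% of trials when allocation is unrelated to that variable. Simulated pass rates were 4.5% to 5.8%, whether the factor was prognostic or a modifier.

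**Step 3: a purely prognostic factor, once in the model**
Approximate z = r/√(1 − r²) × √138, and power = Φ(z − 1.96).
- r = 0.2: 0.204 × 11.75 = 2.40, power about 67%
- r = 0.3: 0.314 × 11.75 = 3.69, power about 96%
- r = 0.5: 0.577 × 11.75 = 6.78, power above 99%

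Simulation gives 64% to 66%, 95% and 100% for the covariate term, and about 5% for the interaction, which is its nominal error rate. With all 172 analysed, r = 0.3 to 0.5 gives 98% to 100%, again against about 5%.

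**Step 4: filter and covariate test together**
- r = 0.2: 0.05 × 0.65 = 3.3% (simulated 3.0%)
- r = 0.3: 0.05 × 0.95 = 4.8% (simulated 4.8%)
- r = 0.5: 0.05 × 1.00 = 5.0% (simulated 5.1%)

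These are rates for one given factor.

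**Step 5: a true modifier**
The filter leaves it out in 1 − 0.05 = 95% of trials. If it is examined, the standard error of the slope difference is about √(1/77 + 1/61) = 0.171, so z = 0.5/0.171 = 2.92 and the interaction has about 83% power. The covariate term depends on how the slopes are placed:
- opposite signs averaging zero: flagged in about 5% of trials (interaction 84% in simulation)
- 0 in control and 0.5 in intervention: flagged in 89% to 90% (interaction 83% to 86%)

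In the second case a significant covariate still cannot be told apart from the prognostic factor in Step 3.

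**The case against.** **The model is not fully specified.** The article gives no dependent variable or list of terms, and it does not exclude interactions. An analysis plan that is not shown could add them. That is fair. However, the point does not rest on a missing detail: the article states the role (covariate) and the filter (significance), and that procedure does not address the first aim.

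**Size of effect may be loose wording for amount of change.** This is possible, and the prognostic aim in the same sentence is legitimate. Even so, predictors of change across all participants are not predictors of benefit from the programme, so the two aims still need separate wording.

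**The filter's meaning is not explicit.** Baseline group difference is the natural reading because the preceding sentences describe such tests. If the authors mean variables related to the outcome, the 5% argument falls away. The filter would then select prognostic variables, and the objection to reading their coefficients as effect modification would remain.

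**The harm is easily overstated.** This stands. A reader might infer that a prognostic factor would be credited with influencing the effect in 65% to 100% of trials. Those rates apply only after entry; the filter reduces them to about 3% to 5% per factor. A reader might also infer that the covariate term always misses a modifier. That requires slopes of opposite sign in the two arms.

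**The sample may be 172, not 138.** Sections 3.1 and 3.2 plan intention to treat with last observation carried forward. The larger sample does not change the pattern.

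**Conclusion.** The point holds in a limited form. Covariate coefficients can show which variables predict functioning. They cannot show which factors are tied to the size of the effect, and selection by baseline group difference does not bring the analysis closer to that question.

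Under the assumed correlations, the covariate and interaction tests give very different answers for a prognostic factor already in the model (about 65% to 100% against 5%). The filter keeps the combined rate at about 3% to 5% for any one factor, and it keeps a true modifier out about 95% of the time. The 5% rate assumes that allocation is unrelated to patient characteristics and that the filter is a baseline comparison.

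Two stronger readings are not supported. The primary (A+B) vs Control comparison is not affected, since this regression is optional and secondary. Nor does the text say that predictors will be reported as explaining who benefits; that is a foreseeable misreading of the results, not a stated intention.

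**What to change.** Separate the two aims in section 3.1.

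- **Size of the effect:** drop the significance filter. Name in advance a few factors already collected at entry, for example baseline SF-36, MADRS, SIMPAQ and 6MWT. For each, fit functioning on arm ((A+B) vs Control), the factor and arm-by-factor. Report the interaction with its confidence interval, labelled exploratory, as the only evidence on this aim.
- **Predictors of functioning:** keep the covariate regression, and describe its coefficients as predictors of functioning only.

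The cost is a change of wording and a few extra model terms, with no new data. The drawback is limited interaction power: at 96 vs 76, a slope difference of 0.3 SD per SD is detected in about 51% of trials. Fewer factors will be declared, and a non-significant interaction should not be read as showing a uniform effect.

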### 3.2. Methods in Analysis to Handle Protocol Non-Adherence and Any Statistical Methods to Handle Missing Data

Last Observation Carried Forward analysis will be used to handle and minimise missing data on the clinical variables.

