#### 2.4.3. Criteria for Discontinuing or Modifying Allocated Interventions

Participants may withdraw from the study for any reason at any time. The investigators also may withdraw participants from the study in order to protect their safety and/or if they are unwilling or unable to comply with required study procedures (i.e., health care providers notice a serious adverse event including hypomania or mixed features).

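### Last observation carried forward (LOCF), the only missing-data method named, biases the arm difference at the later visits and is not reliably conservative

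*Protocol article*

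**What the plan says.** Section 3.2 covers both non-adherence and missing data in its title and consists of one sentence: "Last Observation Carried Forward analysis will be used to handle and minimise missing data on the clinical variables". No other method and no sensitivity analysis is named. Section 3.1 adds: "To analyse efficacy, we will perform intention to treat analysis".

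On the amount of loss, section 2.6 says: "An expected drop-out rate of 20% was set, which resulted according to the initial design in two arms of 76 subjects each". The planned effect is in the same section: "Thus, we computed a Cohen’s d effect size of 0.5 to make estimations more reliable". The main comparison is A+B (48 + 48 = 96) against Control (76), according to sections 2.1 and 2.5.1. Table 2 schedules the SF-36 at baseline, week 4 (T1), week 12 (T2) and week 36 (T3). It schedules the walking, sit-to-stand and handgrip tests at baseline and week 36 only. The Introduction hypothesises that functioning and well-being will improve.

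Section 2.4.3 bears on how data come to be missing: "The investigators also may withdraw participants from the study in order to protect their safety and/or if they are unwilling or unable to comply", continuing "with required study procedures (i.e., health care providers notice a serious adverse event including hypomania or mixed features". The article does not say whether outcomes are still collected after such a withdrawal.

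**The concern.** LOCF enters a participant's last score at every later visit, which is right on average only if scores do not move after people leave. This trial is built on the expectation that they do move. Someone lost before T1 contributes a baseline score at week 36. Someone lost between T1 and T2 contributes a score taken as the one-month programme ends. If the three physical tests count as clinical variables, everyone lost before week 36 is entered with zero change, because baseline is their only other measurement.

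At 20% loss, about 34 of the 172 final values (0.20 × 172 = 34.4) would be supplied by this rule. Section 2.1 hopes the app will maintain benefit in the long term. For those who leave, LOCF assumes the answer to that question. Naming LOCF is a positive choice in this document, not a detail left to an analysis plan.

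**Working it through.** **The plan's own figure.** With d = 0.5, two-sided alpha 0.05 and power 0.80, n per arm = 2(1.960 + 0.842)² / 0.5² = 62.8, so 63. Then 63 × 1.2 = 75.6, so 76 per arm and 152 in total, as stated. The 20% and the 0.5 SD are therefore the plan's working values and are used below.

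**Expected LOCF difference, random loss.** Let e be the true final difference in SD units, c the control-arm change, dI and dC the loss in A+B and Control, and f the average share of the final change reached at the last observation. Then

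LOCF difference = (c + e)[1 − dI(1 − f)] − c[1 − dC(1 − f)].

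Only e = 0.5 and 20% overall loss come from the documents; c, the split by arm and f are assumptions. f = 0 means baseline is carried forward. f = 1/3 means linear change over the three follow-up visits with loss spread evenly before them: (0 + 1/3 + 2/3)/3.

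| e | c | dI / dC | f = 0 | f = 1/3 |
|---|---|---|---|---|
| 0.5 | any | 20% / 20% | 0.40 | 0.43 |
| 0.5 | 0.8 | 30% / 10% | 0.19 | 0.29 |
| 0.5 | 0.8 | 10% / 30% | 0.61 | 0.57 |
| 0 | 0.8 | 30% / 10% | −0.16 | −0.11 |
| 0 | 0.6 | 29.7% / 11.3% | −0.11 | −0.07 |
| 0 | 0.6 | 23% / 17% | −0.04 | −0.02 |
| 0 | any | 20% / 20% | 0 | 0 |
| 0 | 0 | 30% / 10% | 0 | 0 |

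First row, f = 1/3: 0.5 × (1 − 0.2 × 2/3) = 0.433. Third row, f = 0: 1.3 × 0.9 − 0.8 × 0.7 = 1.17 − 0.56 = 0.61. A simulation with random loss and linear change gave 0.43, 0.29, 0.57 and −0.11 for the first four rows.

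**Loss related to the last observed score.** Simulations of 96 against 76 used SD 1, between-visit correlation 0.6 and a natural gain of 0.6 SD by week 36.

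- True effect 0.50 building over time, about 20% loss in each arm: LOCF about 0.43 to 0.44, likelihood 0.50.
- No true effect, 29.7% loss in A+B and 11.3% in Control: LOCF about −0.11 to −0.13, likelihood 0.00.

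**A benefit that fades.** Suppose the effect is 0.50 at T1 and 0 at week 36, with 20% loss in both arms.

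- All loss just after T1: 0.8 × 0 + 0.2 × 0.5 = 0.10.
- Loss spread evenly, with effects 0, 0.50 and 0.25 at the last visit: 0.2 × (0 + 0.50 + 0.25)/3 = 0.05.

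**Power, for scale.** With 96 against 76, SE = √(1/96 + 1/76) = 0.1535.

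- A difference of 0.40 (baseline carried forward, equal 20% loss): 0.40/0.1535 − 1.96 = 0.645, power 74.1%.
- An unbiased 0.50 on 80% of participants: SE = 0.1535/√0.8 = 0.1717, and 0.50/0.1717 − 1.96 = 0.953, power 83.0%.

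**The case against.** The best defence is that the harm is modest at the plan's own figures and that the larger numbers need unsupported assumptions. Much of this stands. The documents give no loss by arm. A and B have six group sessions to attend, but Control carries the band and app for eight months without the programme, so either could lose more. Section 2.12.2 lists retention measures, several of which apply to all arms, and T1 and T2 are by telephone. At 23% against 17% loss the false difference is only about −0.03 SD. An effect fading from 0.50 to 0.25 is estimated at 0.26. Likelihood looks exact partly because the simulated data were missing at random, which it requires. Section 2.5.1 names no primary time point, so reading results at week 36 is itself an assumption. A different visit would not rescue LOCF, though: at T1 every missing score is filled with baseline.

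Four stronger readings are tempting and fail.

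- *Standard errors are too small because filled values are treated as observed.* In simulation the arm comparison's mean model SE was 0.156 against an empirical 0.157 to 0.158, with type I error about 5% under no effect and equal loss.
- *Unequal loss or change over time is each enough for bias.* With random loss, flat scores give none even when loss differs. With no true effect, equal change and equal loss give none.
- *Section 2.4.3 removes people who do not exercise.* The clause concerns study procedures, and its own gloss is a serious adverse event. It does not plainly say that non-compliers are withdrawn.
- *Section 2.4.3 contradicts intention to treat.* It removes nobody from the analysis. LOCF keeps everyone with a baseline in the allocated arm.

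**Conclusion.** The point holds as a criticism of LOCF as the sole method. Under the trial's own hypothesis it does not need unequal loss: with 20% in each arm and an effect that builds, a true 0.50 SD at week 36 becomes about 0.43 to 0.44, or 0.40 if baseline is what is carried forward. A benefit that has vanished by week 36 still shows as about 0.05 to 0.10 SD. These figures rest on the assumed shape of change and timing of loss.

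The false difference of about −0.11 to −0.13 SD rests further on an assumed split of roughly 30% against 11% and a 0.6 SD drift. It shows what could happen and is not a forecast. With Control losing more and scores improving, the error reverses and a true 0.50 can be reported as 0.57 to 0.61. LOCF therefore cannot be defended as conservative. The conclusion does not depend on misstated standard errors, a breach of intention to treat, or a rule that expels non-compliers; the documents support none of these.

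**What to change.** In section 3.2, replace LOCF as the main analysis with a likelihood-based mixed model for repeated measures on SF-36 at T1, T2 and T3. Include baseline SF-36, arm, visit and arm-by-visit, with an unstructured covariance, and take A+B against Control as the main contrast. Add one sensitivity analysis for data not missing at random, for example shifting the unobserved scores by a stated amount in each arm; its details can sit in the analysis plan.

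State also that T1 to T3 outcome assessments continue after non-adherence or after the intervention stops, where consent allows. When a participant should be withdrawn for safety is a clinical matter and is not judged here.

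The cost is wording and a little more analysis work. The SF-36 visits are already scheduled, two of the three are by telephone, and the named statistical package has a mixed-model procedure. The walking, sit-to-stand and handgrip tests have only one follow-up visit, so a repeated-measures model adds little for them; the text should say how their missing week-36 values are handled.

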## 4. Ethics and Dissemination

All the procedures and assessments will follow the accordance of the 1964 Helsinki declaration and its following amendments (64th WMA General Assembly, Fortaleza, Brazil, October 2013). Before any procedure, all the participants will be informed about the study characteristics, and all will be provided with a study information leaflet and written informed consent will be signed. The project has been approved by the IMIM Drug Research Ethical Committee (2019/8816/I).

The study will follow the Consolidated Standards of Reporting Trials (CONSORT) guidelines [31] to describe, report and publish the results. The moment the trial is completed, results will be published in international peer-reviewed journals.

## 5. Trial Status

At the time of the elaboration of this manuscript, the development and testing phase of the IDEApp was finalised after being carried out intensively by three software engineers, three psychologists and one physical medicine specialist. Moreover, the test of the smart band was completed, as well as the co-creation of group contents. In order to be timely aware of improvable issues regarding the programme contents and duration, and to identify IDEApp mistakes and bugs, we are running a pilot with subjects who suffer depressive symptoms. Conclusions from this pilot will be used to fine-tune the programme final version and a “Work in progress” manual will be written to ensure research falsifiability.

